## Methods

### Study design

The LABOR Study is a multi-country, prospective, observational cohort study. It was initially designed to enroll a maximum of 15,000 mother-infant pairs but this figure was modified to 12,000 after recruitment was slowed by the SARS-CoV-2 pandemic at all sites. The study has been registered prospectively with clinicaltrials.gov under identifier NCT04102644 and with the Clinical Trial Registry of India under CTRI/2020/01/022589.

Women are screened for study participation at the time of presentation to the hospital for delivery and followed for 42 days after delivery. The study’s co-primary outcomes are composites of incident maternal and fetal or neonatal adverse events that may be attributed to the intrapartum period. For the mother, the primary composite outcome includes death, hemorrhage, hypertensive disorders, or infection. For the fetus/newborn the primary composite outcome includes intrapartum stillbirth, neonatal death, encephalopathy, or sepsis. The LABOR Study has been designed following the guidelines outlined by the Strengthening the Reporting of Observational Studies in Epidemiology (STROBE) statement (
Figure 1)
^
7
^.

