Approximately seven and 42 days after delivery, LABOR Study staff contact participants by phone (or in person as needed) to assess maternal and neonatal status and interval course. Staff collect information about maternal and neonatal vital status and events since discharge, including signs and symptoms experienced, non-routine clinic or hospital visits attended, diagnoses made, and treatments received.

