### Data analysis and statistical plan

**
*Study outcomes*
**

The primary outcomes of the LABOR Study include a composite maternal outcome of potentially actionable incident adverse events and a composite fetal / neonatal outcome of the same nature (
Table 2). Secondary outcomes include the individual components of the two primary composite outcomes: maternal outcomes including maternal death, incident intrapartum hemorrhage, postpartum hemorrhage, incident hypertensive disorders (eclampsia, severe preeclampsia, preeclampsia, superimposed preeclampsia, severe gestational hypertension), and incident maternal infection (intrauterine inflammation or infection, endometritis), and fetal / neonatal outcomes including intrapartum stillbirth, neonatal death, encephalopathy, and sepsis. The LABOR Study distinguishes between prevalent conditions (those present at the time of enrollment) and incident conditions (those arising after enrollment). Although we identify and assess frequency of prevalent conditions, the primary focus of analytic approaches described below is the characterization and prediction of incident conditions.

**Table 2. T2:** Study outcome definitions.

Maternal Outcomes	
Maternal death	Death of a maternal participant after study enrollment and up to 42 days postpartum, irrespective of cause
Incident intrapartum hemorrhage	Intrapartum vaginal bleeding of ≥ 1000 mL of blood prior to delivery of the placenta
Postpartum hemorrhage	Blood loss of ≥ 1000 mL or any bleeding leading to an adverse event, regardless of mode of delivery, either within the 24 hours after delivery of the placenta (primary) or up to 42 days postpartum (secondary)
Incident eclampsia	New onset of tonic-clonic, focal, or multi-focal seizures in the absence of other causative conditions
Incident severe preeclampsia	New development of systolic blood pressure ≥ 140 mmHg or diastolic pressure ≥ 90 mmHg measured at least 4 hours apart in addition to proteinuria and at least one of the following severe features: thrombocytopenia, renal insufficiency, impaired liver function, pulmonary edema, new-onset cerebral or visual disturbances, or rise in systolic blood pressure to ≥ 160 mmHg or diastolic pressure to ≥ 110 mmHg
Incident preeclampsia	New development of systolic blood pressure ≥140 mmHg or diastolic pressure ≥ 90 mmHg measured at least 4 hours apart in addition to proteinuria in the absence of severe features described above

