Incident superimposed preeclampsia	New development of preeclampsia as defined above in a woman with chronic hypertension
Incident severe gestational hypertension	New development of severe range blood pressure (i.e., ≥ 160 mmHg systolic pressure or ≥ 110 mmHg diastolic pressure) without proteinuria, thrombocytopenia, renal insufficiency, impaired liver function, pulmonary edema, or cerebral or visual disturbances
Incident intrauterine inflammation or infection	Maternal fever and any of the following prior to delivery: fetal tachycardia, maternal leukocytosis, drainage of purulent fluid from cervical os
Endometritis	Presence of two or more of the following on any 2 of the first 10 days postpartum, exclusive of the first 24 hours and with no other recognized cause: maternal fever, abdominal pain, uterine tenderness, purulent drainage from uterus
Fetal / Neonatal Outcomes	
Intrapartum stillbirth	A stillborn fetus weighing at least 500g meeting all of the following criteria at birth: no heart rate, no respirations, absence of pulsation of the umbilical cord, and no definitive movement of voluntary muscles, and in which fetal heart tones were documented on the ultrasound performed at the time of LABOR Study enrollment
Neonatal death	Death of a live-born neonate within 28 days of birth
Neonatal encephalopathy	Live-born neonate weighing at least 1500g that meets one of the following four physiologic criteria: venous cord lactate > 7 mmol/L; 10 minute APGAR < 5; continued need for ventilation at ≥ 10 minutes of life; intrapartum hemorrhage, cord prolapse, severe fetal heart rate abnormality, or uterine rupture, and that demonstrates moderately or severely abnormal neurologic findings in at least three of the following six categories: spontaneous activity, posture, level of consciousness, tone, primitive reflexes, autonomic nervous system.
Neonatal sepsis	Live-born neonate exhibiting one or more signs of early-onset sepsis (i.e., convulsions, tachypnea, severe chest indrawing, nasal flaring, grunting, bulging fontanelle, pus draining from ear, umbilical redness extending to the skin, fever, low body temperature, many or severe skin pustules, lethargy / unconsciousness, or less than normal movement) with a positive blood culture (excluding contaminants) within the first seven days of life

**
*Sample size*
**

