*Descriptive analysis of baseline, intrapartum, and outcome variables.* Common methods for descriptive statistics will be used to examine the distribution of key baseline factors, intrapartum events, and overall outcomes in the study population (e.g., frequencies for categorical variables and measures of centrality and dispersion for quantitative variables). These methods will also be used to examine unadjusted (crude) differences in the distribution of outcomes and intrapartum events by baseline factors. Key baseline factors will include maternal demographics, medical history and obstetrical risk factors, enrollment ultrasound, physical examination and laboratory values collected at admission or enrollment in the study. Intrapartum events will include time-varying variables related to the course of labor (e.g., cervical examinations), provider interventions (e.g., drugs, procedures), and continuous monitoring through fetal and maternal sensors.

*Associations between baseline variables, interventions, and outcomes.* Generalized linear models will be used to estimate the adjusted relative risk with 95% confidence interval of outcomes associated with baseline factors. Covariates (baseline factors) for inclusion in the multivariable models will be identified
*a priori* based on clinical relevance and using causal directed acyclic graphs. We will start by fitting two separate models for binary outcome variables (yes/no) for the composite maternal and fetal / neonatal outcomes, respectively. If baseline factors of interest are found to be associated with the composite outcomes, we will fit models to each of the individual outcome components within each composite (maternal or fetal / neonatal). A similar modeling approach to that used for the composite and individual outcomes will be used to estimate associations between baseline factors (covariates) and key intrapartum interventions such as cesarean delivery.

*Predictive models and risk stratification.* We will develop and validate models to use baseline variables to predict the probability of each outcome. These predicted probabilities can be used to stratify patients by risk. Because of the expected high dimensionality of the data, we will consider the use of dimension reduction techniques such as deep learning autoencoders
^
17

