*infinite horizon* framework, where the decisions can be made recurrently with virtually no limit on the number of decision times. In this case, the estimated treatment regime provides real-time recommended actions based on both baseline and time-varying information rather than at pre-specified time points and is focused primarily on optimizing imminent outcomes. We will utilize reinforcement learning methods developed for infinite horizon problems such as V-learning
^
28
^ and greedy gradient Q-learning
^
29
^.

*Missing data.* As part of ongoing data quality assurance and control procedures, we monitor and promote high completion of key study variables before the end of follow-up, including baseline variables, intrapartum interventions, and variables used to define outcomes. In the analysis phase, we will investigate patterns of missingness and consider the use of multiple imputation or weighted estimation methods, as appropriate, to account for missing data when the proportion of participants missing data is more than 20%
^
30
^. We will also report complete case analyses alongside multiple imputation or weighted estimation to assess the impact of missing data.

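### A recorded in-hospital event settles the composite while loss to follow-up leaves event-free women unknown, so a complete-case analysis of known composites overstates risk even when loss is random

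*Protocol article*

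**What the plan says.** Under Study design the article defines the maternal outcome: "For the mother, the primary composite outcome includes death, hemorrhage, hypertensive disorders, or infection". The fetal/neonatal composite has the same form: stillbirth, neonatal death, encephalopathy or sepsis. Under Statistical analysis both enter as single binary variables: "We will start by fitting two separate models for binary outcome variables (yes/no) for the composite maternal and fetal / neonatal outcomes".

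Table 2 gives the components different windows:
- Intrapartum events and stillbirth are settled by delivery.
- Postpartum hemorrhage counts "either within the 24 hours after delivery of the placenta (primary) or up to 42 days postpartum (secondary").
- Endometritis needs "Presence of two or more of the following on any 2 of the first 10 days postpartum", leaving out the first 24 hours.
- Maternal death is "Death of a maternal participant after study enrollment and up to 42 days postpartum, irrespective of cause".
- Neonatal death is "Death of a live-born neonate within 28 days of birth".

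In-hospital diagnoses are reconciled at discharge. Later events are sought at about seven and 42 days, when staff "contact participants by phone (or in person as needed) to assess maternal and neonatal status and interval course".

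The Missing data paragraph says that patterns will be investigated. Multiple imputation or weighted estimation will be considered, as appropriate, when more than 20% of participants have missing data. It then adds: "We will also report complete case analyses alongside multiple imputation or weighted estimation to assess the impact of missing data".

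The article does not say how the composite is scored for a woman lost after discharge, or whether a woman with an in-hospital event and no later contact is a complete case.

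**The concern.** In an any-of composite, one recorded event settles the answer. Loss after discharge cannot remove a woman whose event was recorded in hospital, but it makes the composite unknown for a woman with no recorded event. Whether the composite is missing therefore depends on its value, even if the loss itself is random.

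A complete-case analysis of known composites keeps all the early events and sheds mostly non-events. At stake are the incidence of both co-primary outcomes and, where loss differs between levels of a baseline factor, the adjusted relative risks. The point matters because complete case is both the named yardstick for the impact of missing data and, in effect, the only analysis at or below the 20% mark.

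**Working it through.** **Inputs.** From the article: the any-of rule, the component windows, and N = 12,000. The article gives no composite rate, later-event rate or loss rate, so there is no figure of its own to reproduce. Assumed: in-hospital risk a = 15% (range 2–20%); later risk b = 1% among those without an in-hospital event (range 0–1%); random loss after discharge L.

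**1. True risk.** a + (1 − a)b = 0.15 + 0.85 × 0.01 = 15.85%. The 95% half-width with 12,000 women is 1.96 × √(0.1585 × 0.8415 / 12,000) = 0.65 points.

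**2. Complete case on known composites.** Estimate = [a + (1 − a)(1 − L)b] / [a + (1 − a)(1 − L)]. The share of composites missing is (1 − a)L.

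| L | Calculation | Estimate | Bias (points) | Bias in half-widths | Composites missing |
|---|---|---|---|---|---|
| 5% | 0.158075 / 0.9575 | 16.5% | 0.66 | 1.0 | 4.25% |
| 10% | 0.15765 / 0.915 | 17.2% | 1.38 | 2.1 | 8.5% |
| 20% | 0.1568 / 0.83 | 18.9% | 3.04 | 4.7 | 17% |

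Across a = 2–20% and b = 0–1%, 20% loss multiplies the risk by 1.16 to 1.24. With a = 5%, b = 1% and 10% loss, the bias is 1.2 half-widths.

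**3. The 20% mark.** At 20% loss, (1 − a)L is 19.6% for a = 2% and 16% for a = 20%. If the proportion is counted on the composite, the mark is not passed, and the complete-case figure could stand alone.

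**4. Complete case as completed follow-up.** With random loss this recovers 15.85%, but it discards known in-hospital events. If loss differs by in-hospital event status (L1 with an event, L0 without), the estimate is [a(1 − L1) + (1 − a)(1 − L0)b] / [a(1 − L1) + (1 − a)(1 − L0)].
- L1 = 5%, L0 = 10%: 0.15015 / 0.9075 = 16.5%.
- L1 = 10%, L0 = 5%: 0.143075 / 0.9425 = 15.2%.

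The bias can go either way.

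**5. Weighting and imputation.** If loss is unrelated to baseline factors, baseline-only weights are constant in expectation and return the estimate of step 2. If the model includes in-hospital event status, women with an event get weight 1 and observed women without one get 1/(1 − L). The estimate becomes a + (1 − a)b, the truth.

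A simulation agrees (12,000 women, 300 replicates, one binary baseline factor, 25% random loss, 22% of composites missing). The true risk was 12.1%. Complete case on known composites gave 15.3%; baseline-only weighting and baseline-only composite imputation each gave 15.2%. With event status added, weighting and composite imputation each gave 12.1%.

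**6. Relative risk** (step 2 estimator in each group, b = 1%).
- In-hospital risks of 20% and 10%, true RR 1.91: equal 20% loss gives 1.88. Loss of 30% in the higher-risk group and 10% in the other gives 2.28; the reverse gives 1.55.
- No true association, a = 15%, two groups of 6,000: loss of 15% and 5% gives 0.1802 / 0.1651 = 1.09. The standard error of log RR is √[Σ(1 − p)/(np)] over the observed women, about 0.042, so a nominal 5% test rejects about 55% of the time. Loss of 8% and 2% gives 1.05 and about 22%.

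**The case against.** The strongest reply is that the article makes none of the choices that produce the bias. It promises to look at missingness patterns and to use imputation or weighting as appropriate. It does not specify baseline-only models, imputation of the composite as one variable, or dropping lost event-free women while keeping lost women with events. Such detail commonly sits in the full protocol or analysis plan. Much of this stands.

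A reader might infer that complete-case, weighted and imputed results are all inflated together, so that their agreement is bound to reassure falsely. The document does not support that. Step 5 shows that weighting and even composite-level imputation recover the truth once in-hospital event status is in the model. The planned comparison would then expose the complete-case bias.

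Three further limits stand:
- It is not only women event-free at discharge who can have a missing composite. In-hospital measurements can be missing too; the calibrated drape, for instance, is specified for vaginal deliveries.
- A relative risk is not inflated by loss as such. Equal loss attenuates it slightly, and unequal loss moves it either way.
- Scoring lost event-free women as no would give a bias of only −(1 − a)Lb = −0.085 points at 10% loss. That is small because b is assumed small, and it is not a complete-case analysis.

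The article also describes measures against loss: locator information, in-person contact as needed, and monitoring of outcome completeness.

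What the reply does not remove is that the article itself names complete case as the comparator and reserves the alternatives for more than 20% missing. No well-specified imputation model helps where none is triggered.

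**Conclusion.** The point holds in a limited form. Complete case on known composites overstates composite risk under random loss: under the assumed 15% and 1%, by 0.66 points at 5% loss, 1.38 at 10% and 3.04 at 20%. Complete case by completed follow-up avoids this under random loss, but wastes known events and is biased when loss depends on in-hospital course. Whether weighting or imputation shares the inflation depends on a model that the article leaves open. Relative risks are affected mainly under differential loss, in either direction.

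The mechanism follows from the outcome definitions; the size rests wholly on assumed rates, and with little loss it would be minor. The choice is worth settling because a better method needs only data already collected.

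**What to change.** State that every enrolled mother–infant pair contributes its recorded status to discharge. Treat the post-discharge components as missing only for those with no recorded in-hospital event. Impute or weight those components conditional on in-hospital course as well as baseline factors, and then derive the composite. Alternatively, estimate cumulative incidence to the end of each window with censoring at last contact. Handle missing in-hospital measurements as a separate step.

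Apply this whatever the percentage missing. If complete case is still reported, say which definition is meant and do not rely on it alone.

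The cost is analysis-plan wording and one extra modelling step. Follow-up is finished, but discharge status and contact results are already recorded, so no new data are needed. The method still assumes that, given in-hospital course and baseline factors, loss is unrelated to later events.

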### Ethical considerations

The study is conducted according to international standards of Good Clinical Practice
^
31
^. The protocol and informed consent documents are approved by properly constituted independent Ethics Committees (ECs) or Institutional Review Boards (IRBs) maintaining Federal Wide Assurances (FWA) with the Office for Human Research Protections (OHRP) at each site. All staff with participant contact receive training on the protection of human research participants prior to conducting any study activities and routinely thereafter
^
32
^.

Participation in the study is voluntary. All study participants are provided a consent form describing the study and providing sufficient information for participants to make an informed decision about their participation in the study. LABOR Study consent forms are translated into local languages and back-translated into English to ensure accurate translation. Potential participants have the choice of undergoing consent in English (all sites); Hindi, Kannada, or Marathi (Belgaum, India); Bengali, Hindi, or Oriya (Balasore, India); Ewe, Ga, or Twi (Ghana); or Nyanja or Bemba (Zambia). Clinical study procedures are conducted according to local standards of routine care. Study staff inform women that they do not have to agree to participate in the study to receive care at the delivery facility even if investigators are affiliated with both the facility and the study.

Investigators make every reasonable effort to minimize risks to participants. We expect that participants in this observational study will be exposed to minimal risk. Physical risks of participation include risks associated with venipuncture or finger prick, which are infrequent and minimized with use of proper technique. Collection of vaginal and rectal samples may also be associated with some discomfort. To reduce the risk of social or psychological harm, we explain the study in detail during the informed consent process and routinely remind participants that they do not have to answer questions that make them uncomfortable. To maintain participant confidentiality, all research-related discussions and informed consent procedures are conducted in a private room or area. All study data, laboratory specimens, and administrative forms are identified by a unique coded number. This unique number is scanned anytime data are captured within the password-protected study tablets. All databases are password-protected and accessible only to members of the study team. 

The study has been approved by the following committees: University of North Carolina IRB, Chapel Hill, NC, USA; University of Ghana College of Health Sciences Ethical and Protocol Review Committee, Accra, Ghana; Korle Bu Teaching Hospital IRB, Accra, Ghana; Institutional Ethics Committee of KLE Academy of Higher Education and Research, Belgaum, Karnataka, India; Institutional Ethics Committee of Fakir Mohan Medical College and Hospital Balasore, Odisha, India; India Research and Ethics Committee, Directorate of Health Services, Odisha, India; Health Ministry Screening Committee of Government of India with Indian Council of Medical Research acting as its Secretariat; University of Zambia Biomedical Research Ethics Committee, Lusaka, Zambia; Zambia National Health Research Authority, Lusaka, Zambia.

### Safety monitoring

At each study contact, study staff evaluate participants for social harms and adverse events. All adverse events occurring after study enrollment are assessed for seriousness and relatedness to study procedures. Study staff document and carefully monitor all serious adverse events occurring in participants whether or not they are related to study participation. The severity of any serious adverse events is graded using the National Institute of Health’s Division of AIDS Table for Grading the Severity of Adult and Pediatric Adverse Events. Study staff are responsible for promptly reporting related adverse events or social harms to the site investigators and the overall study Principal Investigator, who determine if reporting to the appropriate ethics committees is required based on their guidelines. 

### Dissemination of findings

The LABOR Study team will disseminate findings to participants and key stakeholders at local dissemination events and globally at international conferences and in peer-reviewed journals. At the completion of this study, in accordance with the Bill and Melinda Gates Foundation Global Access requirements, research data from participants followed through pregnancy and the postpartum period will be curated and documented, stripped of personal health information, and placed into the public domain. Additionally, the study team welcomes collaboration with others who could make use of intrapartum testing algorithms developed upon study completion. Knowledge generated from this study has the potential to contribute to the development of a suite of tools (which may include diagnostics, devices, and/or software) that can be deployed in low-resource healthcare facilities to substantially improve intrapartum outcomes in low-resource settings worldwide.

